### Quantitative data

We will use Statistical Package for the Social Sciences for Windows (version 19.0; Released 2010; IBM Corp., Armonk, NY, USA) for all statistical analyses. Continuous data are expressed as means with SDs, and categorical variables are presented as absolute numbers or percentages. The normality and homoscedasticity of the data will be checked before each analysis. For comparisons of demographic data between the experimental and control groups, the chi-square test, independent *t*-test, and Mann–Whitney *U*-test will be used as appropriate depending on the features of distributions of the data. As for the training effects on outcomes, a mixed analysis of variance, with time as a within-subject factor and intervention as a between-subject factor, will be performed. *Post hoc* analysis will be performed using the Bonferroni test. *P*-values < 0.05 will be used to indicate statistical significance. If both the data and the residuals are not normally distributed for ANOVA, we will use bootstrapping to get confidence intervals and use those to determine whether effects are statistically significant, rather than using *p*-values directly.

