## Outcomes measured

All participants will be subjected to three evaluations. The first evaluation is at baseline (Time 0), which is before randomization. The second and third evaluations will be performed at the end of the 6^th^ (Time 1) and 12^th^ (Time 2) weeks after the intervention, respectively (Table 2).

**TABLE 2 T2:** Instruments and measures to be implemented for data collection.

Instrument or measure	Outcome	Description	Time point	References
Appendicular skeletal muscle mass index	Diagnostic criterion of sarcopenia. Primary outcome	Measured by bioelectrical impedance analysis. Defined as the appendicular skeletal muscle mass (Kg) divided by the height squared (m^2^)	T0, T1, T2	(49, 52)
Dominant handgrip strength	Diagnostic criterion of sarcopenia. Primary outcome	Measured by JAMAR dynamometer under standard position.	T0, T1, T2	(54)
Gait speed	Diagnostic criterion of sarcopenia. Primary outcome	The participants are asked to walk at a normal speed on a 6-m long corridor without a barrier and the usual gait speed calculated by measuring the time spent by a participant.	T0, T1, T2	(52)
Study of osteoporotic fracture index	Indicator of frailty. Primary outcome	Including three components: (a) a weight loss of ≥ 5% during the preceding year, (b) an inability to rise from a chair five times without using the arms, and (c) an answer of “no” to the question “Do you feel full of energy?”	T0, T1, T2	(57)
Box and block test	Indicator of hand dexterity. Secondary outcome	The number of blocks the participants transferred in 60 seconds from one compartment to the other compartment of the wooden box.	T0, T1, T2	(59)
Biceps and triceps brachii muscle strength of the dominant side	Indicator of muscle strength. Secondary outcome	Using the microFET^®^ 3 to measure the maximal voluntary isometric contraction under standard positions.	T0, T1, T2	(62)
Sonographic thickness of biceps and triceps brachii, quadriceps, and gastrocnemius muscles	Indicator of muscle morphology. Secondary outcome	Using a portable LOGIQ e ultrasound, equipped with a 5-12 MHz linear array transducer, to measure the muscle thickness under standard positions.	T0, T1, T2	(63, 64)
Range of motion of the joints of upper extremity	Indicator of functional movement. Secondary outcome	Using a goniometer under standard positions to measure shoulder flexion, abduction, and external rotation; elbow flexion and extension; forearm supination and pronation and wrist flexion and extension.	T0, T1, T2	(65)

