## Statistical analysis

### Sample size calculation

Since a high-quality study evaluating the effects of a similar intervention on muscle strength, physical activity, and function was unavailable when we wrote our protocol, we used previous results from one study using augmented reality (AR)-based exercise for one of our primary outcome measures (ASMMI) (72) for this power calculation. The effect size of a similar study for the AR-based intervention is high (0.71). Based on G*Power (version 3.1.9.2, for Windows), at least 18 observations in each group should be recruited by detecting a difference of 2 standard deviations (SD) of the ASMMI between the groups with a power of 80% and alpha of 5%, and the effect size is determined to be high (*F*-test family, 0.4) (73). To account for an expected dropout rate of 40%, given that most participants in the LTCFs have comorbidities, we decided to increase this number to a group size of 26. Thus, the aim will be to include at least 52 patients in the study.

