Supervised exercise is safe for frail older adults (85). Only one well-trained assistant will be required to supervise the entire exergame-based exercise procedure in this project. Many participants can play the game simultaneously if the number of Nintendo Switch and RFA is sufficient, which is time- and manpower-consuming. However, this study protocol has some limitations. First, this study used the convenience sampling method because recruiting older adults who regularly participate in LTCFs publicly is difficult and impractical. This project might be less representative, even though the minimum estimated sample size can be met. The results of this study should be applied with caution and could only be generalizable to similar populations. Second, the exergame-based exercise and outcome measures only lasted 3 months. This duration might be insufficient to observe an increase in the muscle mass of older patients. However, given that an intervention period of more than 3 months might lead to a higher attrition rate of the participants, particularly for those in LTCFs with several comorbidities, we will also measure muscle morphology using sonography to detect any earlier change in muscle parameters, and we still suggest a 3-month protocol. Third, to our knowledge, this project is the first study to evaluate the effectiveness of using RFA among elderly individuals living in LTCFs. No established protocol for training with RFA could be followed. Although the entire exercise prescription is based on the guidelines for older adults by the ACSM, we cannot ensure that the protocol for the current exergame-based exercise is ideal. Fourth, individualized setting and progression of the exercises automatically are the features of using RFA to train elderly individuals. However, this project can only measure the exercise intensity by RPE. The investigators cannot confirm the exact resistance provided by the Ring-Con during each training session.

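### The planned mixed ANOVA uses only participants with all three visits: at the plan's own 40% dropout, and without imputation, about 31 of 52 randomised

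*Protocol article*

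**What the plan says.** The Quantitative data section names a single method for the effect of training on outcomes: "a mixed analysis of variance, with time as a within-subject factor and intervention as a between-subject factor, will be performed". The software is given as "We will use Statistical Package for the Social Sciences for Windows (version 19.0"). The only fallback offered is bootstrapping, and its trigger is non-normality, not missing visits.

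The Outcomes measured section sets the visits: "All participants will be subjected to three evaluations", at baseline (T0), week 6 (T1) and week 12 (T2). The same method therefore serves all four primary outcomes: ASMMI, dominant handgrip strength, gait speed and the SOF index.

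The Sample size calculation section requires that "at least 18 observations in each group should be recruited". It then introduces the allowance with "To account for an expected dropout rate of 40" per cent, giving comorbidity as the reason, and says "we decided to increase this number to a group size of 26", so that "the aim will be to include at least 52 patients in the study". The limitations paragraph of the discussion returns to attrition: "an intervention period of more than 3 months might lead to a higher attrition rate of the participants".

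**The concern.** The word mixed here refers to mixing a within-subject and a between-subject factor. It does not denote a likelihood-based mixed model, and the fallback is also worded in terms of ANOVA. A classical analysis of this kind needs T0, T1 and T2 on every participant. Someone with no T2 value leaves the analysis altogether, together with the T0 value and any T1 value already collected.

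That would matter little with few losses, but the plan expects to lose two in five. It attributes the losses to comorbidity, in a trial whose primary outcomes are muscle mass, strength, walking speed and frailty. The reason for leaving may therefore be related to what is measured. The arms also differ in what they ask of people: one does supervised exercise at a target of 13 on the Borg scale, the other continues its usual activities, and neither participants nor staff can be blinded. If the losses are selective in a way that differs between arms, those who remain are no longer comparable as randomised.

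**Working it through.** **Inputs from the article.** 18 evaluable per group; effect size f = 0.4; power 80%; alpha 5%; three measurements; 40% dropout; 26 per group, 52 in total. **Assumption.** Within-person correlation ρ = 0.5 for the power figures; the article gives none.

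**1. Reproduce the plan's sample size.** For the between-groups F-test with N participants and m measurements, the noncentrality is λ = f² × N × m / (1 + (m − 1)ρ). With N = 36, λ = 0.16 × 36 × 3 / 2 = 8.64 on 1 and 34 degrees of freedom, and power is 0.815. With N = 34 it is 0.791. So 36 in total, 18 per group, is reproduced. The inflation is reproduced as 18 × 1.4 = 25.2, rounded up to 26. Either way, the plan sizes the trial as if dropouts contribute nothing.

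**2. Number analysed under the planned method.** 52 × (1 − 0.40) = 31.2, about 31, or 26 × 0.6 = 15.6 per group. About 52 − 31 = 21 randomised people would be left out. This count does not depend on ρ. It is an expected figure, and anyone who missed only T1 would lower it.

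**3. Data unused.** The article does not say when the 40% leave. If all leave before week 6, no T1 values are lost. If all leave after week 6, T1 values from about 21 people are lost. The range is 0 to about 21.

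**4. Bias, by simulation.** Assumptions: no true effect, 26 per arm, about 40% lost after T1, ρ from 0.5 to 0.9, 4,000 replicates per scenario. The completer estimate is the between-group difference in T0–T2 change.

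*Loss related to T0–T1 decline in the intervention arm only:*

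| Log-odds of loss per SD of decline | ρ = 0.5 | ρ = 0.7 | ρ = 0.9 |
|---|---|---|---|
| 1.0 | +0.172 SD | +0.132 SD | +0.075 SD |
| 1.5 | +0.229 SD | +0.171 SD | +0.103 SD |

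The change-score test rejected in 7.4–9.2% of replicates. Independent repeats gave +0.07 to +0.22 SD and 7–10%. In the repeat that also examined the planned group × time F-test, it rejected in about 12–18%. The positive sign follows from placing the selective loss in the intervention arm; placing it in the control arm would reverse it.

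*Same mechanism in both arms:* bias at most about 0.01 SD, type I error 4–6%.

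*An estimate using T0 and T1 of everyone, one-arm mechanism:* bias at most 0.007 SD. Loss in these runs depends only on observed T0 and T1 values, which is the condition (missing at random) under which such an estimate is unbiased.

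**5. Precision at T2.** At ρ = 0.5 and log-odds 1, the standard deviation of the T2 estimate was 0.36 for both approaches. No gain at T2 is shown. Any gain would lie mainly at T1, where the unused values return.

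**The case against.** The strongest reply is that a completers analysis is inferred. The article does not state one: it names no completers or per-protocol set and does not mention deletion of incomplete cases. A full protocol or analysis plan that is not shown could impute missing values and then run the same ANOVA. This stands as a condition on the conclusion. It does not remove the point, because what the article fixes is a method poorly suited to the dropout it predicts, and its sample-size step treats dropouts as contributing no data.

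A reader might go further in several directions that the documents do not support:

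- **That T1 data from some 21 people will certainly be thrown away.** No timing of dropout is given, so this is only the upper end of the range.
- **That the result will be tilted towards the exergame.** The article's stated reason for dropout, comorbidity, applies to both arms. The control arm is not purely sedentary either: its standard care includes calisthenics led by a therapist, and both arms keep their usual rehabilitation. Selective loss in one arm only is possible, but nothing in the article shows that it will occur.
- **That the ANOVA causes the fall from 36 evaluable to 31.** That shortfall comes from multiplying by 1.4 where division by 0.6 was needed (18 / 0.6 = 30 per group). It is a separate error. Correcting it would restore the number of completers and still leave a comparison of completers.
- **That the alternative model is free of bias.** It is so only under missing at random. If people leave because of acute illness after week 6 that T0 and T1 do not foretell, that model is biased too.

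**Conclusion.** The point holds in a conditional form. As written, and without imputation, the only stated analysis of training effects would rest on about 31 of 52 randomised participants at the plan's own dropout rate. The count follows from the article's figures alone.

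The bias is a risk of uncertain size. It runs from about zero, when loss works the same way in both arms, to about 0.07–0.23 SD with type I error of about 7–10% (change-score test), when loss follows decline in one arm only. These figures rest on the simulation assumptions listed above, and the direction cannot be known in advance. The case for change rests on comparing the groups as randomised and on using data already collected. A gain in precision at T2 is not part of it. Grade: should be fixed.

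**What to change.** For the continuous outcomes, replace the mixed ANOVA with a likelihood-based linear mixed model for repeated measures, available as the MIXED procedure in the same package. Specify group, visit, group × visit and an unstructured within-person covariance. Include all randomised participants with available data, analysed as randomised. Keeping T0 in the outcome vector with a common baseline mean also retains those who have T0 only.

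The SOF index classifies people as robust, pre-frail or frail, so it needs an ordinal counterpart in place of a linear model.

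State that the T1 and T2 evaluations, already scheduled for all participants, are attempted even after someone stops training. Report the completers ANOVA as a sensitivity analysis.

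The cost is a few sentences of wording and slightly more analysis work, with no visits beyond those scheduled. The downside is reliance on missing at random, which measuring people after they stop training helps to limit.

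### Baseline is a level of the time factor instead of a covariate: a group main effect over T0–T2 would be diluted, and the interaction test loses some efficiency

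*Protocol article*

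**What the plan says.** Protocol article, Quantitative data: training effects on outcomes are assessed by a mixed ANOVA "with time as a within-subject factor and intervention as a between-subject factor". For follow-up, "analysis will be performed using the Bonferroni test". Significance is P < 0.05. No covariate appears.

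Protocol article, Outcomes measured: there are three evaluations, and "The first evaluation is at baseline (Time 0), which is before randomization". The other two fall at the end of weeks 6 (T1) and 12 (T2). Table 2 lists T0, T1 and T2 for every outcome. The Quantitative data section does not spell out the levels of the time factor, but T0, T1 and T2 are the only set that the article offers.

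Protocol article, Sample size calculation: "at least 18 observations in each group should be recruited", derived in G*Power "with a power of 80% and alpha of 5" per cent. The G*Power procedure, the number of measurements and the within-person correlation are not given.

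**The concern.** A mixed ANOVA over T0, T1 and T2 gives a group effect, a time effect and a group-by-time interaction. T0 precedes randomisation, so its expected group difference is zero (the observed difference will vary by chance). A group main effect that averages over T0 therefore estimates less than the effect of training. The interaction is not averaged down in this way, but it spends two degrees of freedom on any difference in profile, and it uses T0 in the manner of a change score, which is less precise than using it as a covariate.

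The trial is small: 18 evaluable per group are planned, and 26 less 40% dropout leaves about 16 (26 × 0.6 = 15.6). T0 is already measured for every outcome. Leaving it unused as a covariate gives up precision that costs nothing.

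**Working it through.** **Inputs from the Sample size calculation section**
- Alpha 5%, power 80%, 18 evaluable per group.
- Effect size used: "the effect size is determined to be high (*F*-test family, 0.4"; for two groups d = 2f = 0.8.
- Source study: "The effect size of a similar study for the AR-based intervention is high (0.71". Its metric is not stated; it is taken here as a difference at T2 in SD units.
- The same section also gives a 2 SD difference, which does not match f = 0.4; it is not used here.

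**Assumed, because the article gives no figure:** SD 1 at each visit; equal correlation ρ between visits (0.5, 0.7, 0.9); two trajectories of the group difference at (T0, T1, T2), namely linear (0, d/2, d) and early (0, d, d).

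**Step 1. The planned 18 per group.** For the between-group main effect in a repeated-measures ANOVA with m measurements and N participants in total, λ = f²·N·m / [1 + (m−1)ρ], with 1 and N−2 df. With f = 0.4, m = 3, ρ = 0.5 and N = 36: λ = 0.16 × 36 × 3 / 2 = 8.64, power 0.815. N = 34 gives 0.791. So 36 in total, or 18 per group, is reproduced, but m and ρ are inferred. Other options give different totals: the interaction with m = 3 and ρ = 0.5 gives 12, the main effect with m = 2 and ρ = 0.5 gives 40, and a one-way ANOVA gives 52. The calculation that fits presumes the full effect at all three visits, T0 included.

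**Step 2. Size of the dilution.** The mean difference over T0–T2 is (0 + d/2 + d)/3 = d/2 if linear, and (0 + d + d)/3 = 2d/3 if early. With d = 0.71 these are 0.355 and 0.473.

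**Step 3. Power with n = 18 per group, d = 0.71**
- Main effect: λ = (n/2)·(mean difference)² / [(1+2ρ)/3], df 1, 34.
- Interaction: λ = (n/2)·Σ(difference at each visit − mean difference)² / (1−ρ), df 2, 68. The sum is 0.252 if linear and 0.336 if early.
- T2−T0 change: λ = (n/2)·d² / [2(1−ρ)], df 1, 34.
- T2 adjusted for T0: λ = (n/2)·d² / (1−ρ²), df 1, 34 (using 33 df moves power by about 0.1 point).

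Example, ρ = 0.5, linear: main effect λ = 9 × 0.355² / 0.667 = 1.70; interaction λ = 9 × 0.252 / 0.5 = 4.54; change λ = 9 × 0.504 / 1 = 4.54; adjusted λ = 9 × 0.504 / 0.75 = 6.05.

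| Test | Trajectory | ρ = 0.5 | ρ = 0.7 | ρ = 0.9 |
|---|---|---|---|---|
| Group main effect T0–T2 | linear | 25% | 21% | 19% |
| | early | 39% | 34% | 30% |
| Group-by-time interaction | linear | 45% | 67% | 99% |
| | early | 57% | 80% | 99.9% |
| T2−T0 change | either | 54% | 76% | 99.6% |
| T2 adjusted for T0 | either | 67% | 83% | 99.7% |

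**Step 4. What the covariate itself adds.** Adjusted T2 against T2−T0 change, both with one numerator df: about 12, 6 and 0 points at ρ = 0.5, 0.7 and 0.9. The rest of the gap to the interaction comes from testing one time point instead of a profile.

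**Step 5. Sensitivity.** With d = 0.8 the main effect has 23–48% power over the same grid. With 16 per group, d = 0.71 and linear build-up, the main effect has 22 / 19 / 17%, the interaction 40 / 61 / 98% and the adjusted T2 difference 61 / 78 / 99%.

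**The case against.** The strongest reply is that the plan never makes the group main effect the efficacy test. In a model meant to show training effects, the group-by-time interaction is the natural reading, and T0 does not dilute it. This stands. A reader might infer that the plan as written dilutes the treatment effect, or that the trial has only some 20–40% power; the article supports that only on the condition that the main effect is the test. The match with 18 per group makes the main effect a plausible basis for the sample size, but it needs two unstated inputs, and a sample-size option does not by itself fix the test.

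The loss against the interaction also depends on unknowns. With the full effect at T1 it is 3 points at ρ = 0.7 and slightly reversed at ρ = 0.9. This stands too, and is why a range is given.

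A reader might also fault the article for not naming the deciding effect or time point. That is commonly left to a statistical analysis plan, which is not shown, so it is no finding in itself. Nor is a free choice of test after seeing the data shown: the Blinding section says that the person analysing the data is blinded, which limits it.

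Finally, the SD-based figures do not describe the SOF index, a count of three components. What remains is that the article itself fixes the model, with T0 as a level and no covariate.

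**Conclusion.** The concern holds in conditional form. The article enters pre-randomisation T0 as one of three time levels and does not adjust for it. If the T0–T2 group main effect is taken as the treatment test, the effect shrinks to one half or two thirds of its T2 size, and power is about 19–39% against the planned 80%. If the interaction is the test, the analysis is valid, and its shortfall against the baseline-adjusted T2 difference is 10–22 points at ρ = 0.5, 3–16 points at ρ = 0.7 and negligible at ρ = 0.9. All of this rests on 18 per group, 0.71 read as an SD difference at T2, equal correlations, and assumed values of ρ and trajectory; it applies to the continuous outcomes only. The change is worth making, but the plan does not fail without it.

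**What to change.** In Quantitative data, state that for each continuous outcome the efficacy analysis is the between-group difference at T2, adjusted for that outcome's T0 value, with a 95% CI, from a model with T1 and T2 as responses. Make the T1 difference secondary. For the SOF index, use a baseline-adjusted model suited to an ordinal 0–3 score. State that the group main effect over T0–T2, the time effect and within-group pre–post tests will not be used as evidence of efficacy.

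The cost is wording. T0 is already collected for every outcome, so no visit, measurement or participant is added.

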## Anticipated results and discussion

This study protocol describes the design of an RCT that evaluates the clinical effect of the exergame-based exercise delivered *via* RFA among older adults in LTCFs. Individuals around the world live longer nowadays, and many countries will become a super-aged society soon. Preventing and delaying the loss of intrinsic capacity and functional ability of older adults and helping them age successfully are crucial for us (74). Elderly individuals living in LTCFs are more prone to geriatric syndromes, such as frailty and sarcopenia, than those living in the community. Moreover, many LTCFs lack healthcare professionals, particularly those in rural regions. This project aims to study whether we can use exergame-based exercise as an alternative to previous manpower-consuming therapies in LTCFs. Given that the concepts of frailty and sarcopenia are multifactorial and their definitions vary, this study focuses on the parameters of muscle and functional performance.

This project is unique as the exergame-based exercise is delivered *via* RFA. Similar to other exergames, RFA uses a gamified approach and immersive scenarios to motivate the player by role-playing (31). It could provide both visual feedback from the screen and sensory feedback from the Ring-Con. Apart from other exergames, with its featured Ring-Con, RFA could be considered a multicomponent exercise, combining PRT and aerobic exercises for strength, balance, and muscle stretching. Studies have evaluated the effectiveness of PRT among community-dwelling older adults and proven that it is easily available at a low cost and effective in improving physical function and strength (10, 75). Therefore, we are looking forward to the clinical effectiveness in improving the muscle parameters after this study.

Another feature of using RFA to deliver exergames is that it could set up the initial amount of exercise that must be performed in each stage and adjust it progressively and automatically depending on the performance of the player. Therefore, the progression for the exercise prescription might be individualized, and it is time- and manpower-saving given that it could be modified by the machine. The ACSM suggests increasing intensity over time to maintain the intensity of the exercises at moderate levels (41–60% of 1 RM for resistance exercise and Borg RPE 12–14 for aerobic exercise) (76). Therefore, the study protocol sets the target intensity of the exergame-based exercise at Borg RPE 13 and leaves the weight intensity to Nintendo Switch itself. Although it is practical to do so in real-world settings, and it is safer for the elderly to perform PRT by squeezing or stretching the Ring-Con, one limitation is that we cannot confirm whether the weight intensity given by the Ring-Con is sufficient at moderate levels.

Given that many elderly individuals in LTCFs use a wheelchair for community ambulation because of poor muscle endurance even though they can walk for a short distance to complete gait measurements (40), the exergame-based exercise of this project focuses on training the upper extremities and trunk. By doing so, the participants could be trained in the sitting position to avoid the potential risk of falls. Therefore, most outcomes of this project, including the HGS, MVIC, sonographic thickness of the biceps and triceps brachii muscles, ROMs of the joints of the dominant upper extremity, and BBT, are measured to evaluate the training effects. A study has proven that aging can attenuate the hypertrophic response of muscle groups to RT (77). Contrary to the findings from healthy young adults, in whom neural factors account for a larger proportion of the initial strength increment and muscle hypertrophy becomes the dominant factor after the first 3–5 weeks (78), the effect of muscle training may entirely depend on the neuromuscular adaptation among older adults after an 8-week training course (79). Given the results from the classical studies by Moritani and deVries and considering that the project lasted only 3 months, we measured not only the MVIC but also the sonographic thickness to see whether some early morphological changes in the trained muscles could be detected earlier.

The primary outcomes in this protocol are the criteria to diagnose frailty and sarcopenia. Therefore, this project will measure the gait speed through the exergame-based exercise, which focuses on the upper extremities and trunk only. Walking is a complex movement that requires several functional tasks, such as ROMs, velocity, position, and trained muscles (80). The participants must balance in different positions, such as leaning forward, forward reaching, side shuffle, and lateral shifting, to use the RFA. Those movements might occur at the trunk/hips/knees, although the protocol does not allow the performance of PRT on the lower extremities. Granacher et al. demonstrated that the ability of older adults to rise from a chair, ambulate, and make turns improves after 9 weeks of core muscle strength training (81). Park et al. observed that walking speed increased after a sitting boxing program focusing on upper extremity stretching and strengthening for 6 weeks (82). Both studies have proven that strengthening programs can also induce adaptive processes, particularly in the neuromuscular system, thereby enhancing balance performance and functional mobility. Moreover, interlimb and intralimb segment coordination are important for bipedal human gait. Arm swing in the human gait cycle plays an active role in maintaining body posture. The gait speed increases when the amplitude of the arm and leg is increased (83). Given the aforementioned three main reasons, the exergame-based exercise in this study might increase gait speed.

By presenting with heterogeneity, one recent systematic review with the recruitment of 15 eligible RCTs found that exercise not only has a positive effect on physical outcomes but also improves QoL and ADLs in elderly individuals (84). Therefore, in addition to measuring the clinical effects of the exergame-based exercise on parameters of muscle and functional performance, this protocol also includes the QoL and ADL as secondary outcomes. The SF-36 is used to indicate the HRQoL because it is a validated self-assessment generic health survey with a reliable intraclass correlation coefficient (70). KC-T will be used to indicate the ADL since its usability in practice in real-world settings in Taiwan has been proven (68), and it is widely used in LTCFs. Moreover, both the SF-36 and Kihon checklist have Taiwanese versions, which are important when measuring the QoL and ADL because the values toward QoL and ADL vary from culture to culture.

No cutoff value of available cognitive measurements allows us to screen who is suitable for exergames. Most studies on exergames in the elderly recruited participants with sufficient cognition levels to understand the orders and procedures required in the game (36). Many older adults in LTCFs have some cognitive deficits, though the degree varies in Taiwan (68). Exergames have therapeutic effects on cognition among older adults (34, 36). Although the manner of play varies among exergames, there are some commonly shared concepts. Exergame environments provide an extra spatial feature. Players confront challenging tasks with visual and auditory stimuli, cues, and feedback. Immersion into a virtual environment also redirects the player’s experiences to improve attention restoration, reduce stress, and promote cognitive rehabilitation. Furthermore, exergames require players to make decisions during the game. Exergames delivered *via* RFA provide all aforementioned features, and we expect that the cognitive level of the elderly in LTCFs improves after the training.

Supervised exercise is safe for frail older adults (85). Only one well-trained assistant will be required to supervise the entire exergame-based exercise procedure in this project. Many participants can play the game simultaneously if the number of Nintendo Switch and RFA is sufficient, which is time- and manpower-consuming. However, this study protocol has some limitations. First, this study used the convenience sampling method because recruiting older adults who regularly participate in LTCFs publicly is difficult and impractical. This project might be less representative, even though the minimum estimated sample size can be met. The results of this study should be applied with caution and could only be generalizable to similar populations. Second, the exergame-based exercise and outcome measures only lasted 3 months. This duration might be insufficient to observe an increase in the muscle mass of older patients. However, given that an intervention period of more than 3 months might lead to a higher attrition rate of the participants, particularly for those in LTCFs with several comorbidities, we will also measure muscle morphology using sonography to detect any earlier change in muscle parameters, and we still suggest a 3-month protocol. Third, to our knowledge, this project is the first study to evaluate the effectiveness of using RFA among elderly individuals living in LTCFs. No established protocol for training with RFA could be followed. Although the entire exercise prescription is based on the guidelines for older adults by the ACSM, we cannot ensure that the protocol for the current exergame-based exercise is ideal. Fourth, individualized setting and progression of the exercises automatically are the features of using RFA to train elderly individuals. However, this project can only measure the exercise intensity by RPE. The investigators cannot confirm the exact resistance provided by the Ring-Con during each training session.

If the findings of this study show that the exergame-based exercise *via* RFA could improve the parameters of muscle and functional performance, the training method should be implemented as a treatment option for all older individuals living in LTCFs, particularly for those in rural regions with lesser healthcare resources. A successful exergame-based exercise would provide benefits beyond muscle strength, muscle mass, and ADLs of the elderly because it would also enhance the HRQoL or even help the elderly age gracefully. We expect that the protocol will be useful and practical to implement in real-world settings. With the positive results of this protocol, further larger studies could be conducted to examine whether the exergame-based exercise *via* RFA could be a treatment alternative to time- and manpower-consuming therapies currently applied in LTCFs.

